## Abstract

**Background:**

Financial hardship and health-related social needs (HRSNs) are prevalent among cancer patients and contribute to disparities in outcomes. Addressing these issues can reduce harm, yet routine screening and intervention remains underutilized. Navigator-led interventions such as combining out-of-pocket cost (OOPC) communication and financial navigation (CostCOM) have shown promise, but face implementation barriers due to navigator shortages. It is unclear whether financial education and resource access alone (FinEd), without navigator support, can meet patients’ needs.

**Method:**

We propose a three-arm pilot randomized controlled trial comparing FinEd, enhanced usual care (EUC) and CostCOM in 90 newly diagnosed cancer patients undergoing systemic or radiation therapy who screen positive for financial hardship or HRSNs. FinEd includes (1) a list of local/national resources for financial and HRSNs support, and (2) educational materials on health insurance, delivered via mail and a one-time phone/video session with a study coordinator. CostCOM includes (1) systemic therapy OOPC estimates, (2) financial navigation to identify assistance programs, and (3) financial counseling, delivered over two phone/video sessions by a financial navigator. EUC includes study-specific identification of financial hardship and HRSNs. Our goals are to investigate preliminary efficacy of the three arms within six months post-randomization on cost-related care non-adherence (primary outcome), treatment completion, missed appointments, financial worry, material hardship, insurance literacy, quality of life, and sleep quality. We will evaluate patient experience with FinEd using qualitative interviews.

**Conclusion:**

This study will support feasibility for a larger trial, and provide initial efficacy estimates comparing FinEd vs. EUC vs. CostCOM in improving cancer outcomes.

**Trial registration:**

Clinicaltrials.gov NCT06430840; registered 5/24/2024; https://clinicaltrials.gov/study/NCT06430840?cond=NCT06430840&rank=1.

## Introduction

1

Financial hardship and health-related social needs (HRSN) are significant health equity issues affecting patients in the United States. Approximately 42-56% of cancer survivors report financial hardship and 15-60% report HRSNs [[1], [2], [3], [4], [5], [6], [7]]. Financial hardship is characterized by three domains: cost-related care nonadherence, material hardship (e.g., medical debt), and financial worry [1]. HRSNs are characterized by insecurity about food, housing, transportation, and utilities [8,9]. Both financial hardship and HRSNs contribute to disparities in care access, cancer outcomes, and overall survival, as well as quality of life (QOL) and sleep disturbance [6,8,15]

**Fig. 1 fig1:**
[figure not shown]
Study schema.

Routine screening for financial hardship and HRSNs in clinical oncology practices is limited by staffing constraints and absence of standardized screening tools [10]. While several screening tools have demonstrated feasibility and acceptability [[16], [17], [18]], and over 70% of community oncology practices report available services to screen for and respond to financial hardship and HRSNs [19], screening remains uncommon as availability of the service does not equate coverage of all patients at risk. Notably only 16.6% of cancer patients were actually screened in a retrospective analysis of a single comprehensive cancer center [10]. This gap highlights the need for approaches that reduce staff burden while addressing patient needs.

Beyond screening, responding to identified needs is also limited by staffing and lack of referral systems [18]. Interventions such as financial navigation, financial education, and cost communication have been proposed [[20], [21], [22]]. While financial navigation improved financial worry among high-risk patients [19], its implementation is constrained by the need for trained navigators. As financial hardship is associated with low financial health literacy [22] and financial self-efficacy [23], financial education may also be effective. However, prior financial education studies have also relied on delivery by navigators [23,24]. It remains unclear whether navigator-free approaches—such as self-directed educational materials and financial resources—are more effective than usual care, or how they compare to active financial navigation in improving financial hardship and quality of life. Further, financial hardship has been associated with poor sleep quality, including increased insomnia severity and sleep disturbances among cancer patients [15]. Given that financial stress is a recognized psychosocial stressor capable of activating physiological pathways that interfere with sleep, interventions targeting financial hardship may plausibly improve sleep outcomes as a secondary benefit. However, the extent to which financial hardship-focused interventions may improve sleep quality among cancer patients remains largely unexplored. Therefore, sleep quality was included as an outcome in the present pilot study to assess whether reductions in financial hardship are accompanied by improvements in this dimension of patient well-being.

The CAN-ASSIST trial is a three-arm pilot randomized controlled trial testing the preliminary efficacy of navigator-free financial education and resources (FinEd) vs. enhanced usual care (EUC) vs. out-of-pocket cost communication and financial navigation (CostCOM) on domains of financial hardship (care non-adherence, material hardship, and financial worry), financial health literacy, quality of life, and sleep quality among cancer patients on systemic treatment who screen positive for financial hardship and HRSNs [15].

## Objectives

2

We will investigate the preliminary efficacy of FinEd vs. EUC vs. CostCOM within six months after randomization on patient-reported cost-related cancer care non-adherence (primary outcome), electronic medical record (EMR)-abstracted treatment completion, missed appointments, patient-reported financial worry, material financial hardship, health insurance literacy, QOL, and sleep quality as well as objectively measured sleep quality (secondary outcomes). We will further describe FinEd arm patient experience with the FinEd intervention using mixed methods (implementation outcome).

## Materials and methods

3

### Trial design

3.1

CAN-ASSIST is a pilot, parallel, 3-arm randomized controlled trial with randomization at patient-level (See Fig. 1). There will be no blinding of participants or study coordinators. The study has been approved by the Institutional Review Board (IRB), and this protocol is reported in accordance with the Standard Protocol Items: Recommendations for Interventional Trials (SPIRIT) guidance [25].

### Study site

3.2

The study takes place in the six academic and community oncology clinics associated with a single comprehensive cancer center in Southern California. The catchment area of this cancer center includes a diverse population with 43% White, 22% Asian, 2% African American, 14% multi-racial, and 19% other races. Furthermore, 34% of the county's population are Hispanic, 30% are immigrants, and 43% are not a US citizen. A total of 45.2% speak languages other than English at home, with 70% speaking English or Spanish [26].

### Eligibility criteria

3.3

Patients with the following characteristics are eligible for the study: 1) Age of 18 years or older, 2) being able to answer surveys and interact with the study team in English or Spanish, 3) a new cancer diagnosis of any type or stage by histology in the last 120 days, 4) having started systemic cancer treatment or radiation therapy, 5) being treated in our cancer center oncology clinics, 6) screen positive for financial hardship or HRSNs (see Section 3.4). The 120-day window was selected because prior research shows patients prefer early financial screening [27]. Financial hardship peaks in the first few months after early-stage cancer diagnosis and improves thereafter, [28,29], whereas it worsens over time in metastatic cancer [30], thereby justifying the use of 120 days since diagnosis as an inclusion criterion.

The exclusion criteria included Eastern Cooperative Oncology group (ECOG) performance status more than 2, participation in other therapeutic clinical trials that cover the cost of treatment, prior history of cancer diagnosis or treatment in the last 24 month except for in situ cancers, non-melanoma skin cancers, and breast cancers diagnosed more than 24 months ago who were only receiving hormonal treatment in the last 24 months.

### Pre-screening and outreach

3.4

Potentially eligible patients will be identified from oncology clinic rosters using a combination of weekly automatic inquiry of electronic medical records (EMR) using institutional IT data warehouse, manual review of clinic schedules, and collaboration with oncology care teams engaged in the study. Patients will be approached both in person by bilingual research coordinators during oncology clinic visits and remotely through email outreach via REDCap.

Interested patients will receive a study information sheet and be asked to complete a brief, 2-min screening survey. This survey will collect basic demographic information (age, gender, race, ethnicity, insurance status) and include five questions to screen for financial hardship and HRSNs. These questions include Item #12 of the Comprehensive Score for Financial Toxicity (COST]) “My illness has been a financial hardship to my family and me” [31,32] and four screening questions addressing food, housing, transportation, and utility insecurity, derived from the Centers for Medicare & Medicaid Services Accountable Health Communities (AHC) Health-Related Social Needs Screening Tool [33]. Patients who endorse any of the four HRSN-related items or financial hardship will be considered eligible for study participation.

To ensure accessibility, the survey will be available in both English and Spanish and can be completed through various convenient methods: in-clinic using paper or electronic forms, online via REDCap email, or by phone with assistance from a bilingual study coordinator.

### Baseline survey

3.5

Eligible patients will receive a study overview by a study coordinator and provide a signed, dated informed consent on paper (in person or via mail) or electronically (via REDCap). Patients will then be asked to complete a 30-min baseline survey, available in English or Spanish, and in paper or electronic format based on their preference.

The survey includes validated measures to assess patient-reported receipt of cancer supportive services as part of usual care (i.e., cost communication, financial counseling, financial assistance), cost-related care non-adherence [34], material hardship [34], financial worry [31,32], QOL [35], health insurance literacy [36], subjective sleep quality [37], as well as questions about patients’ demographics, insurance, single item health literacy [38], zip code (to assess neighborhood socioeconomic status), and presence of other comorbidities. Participants who complete the baseline survey will receive a $20 gift card.

### Randomization

3.6

Consented patients who complete the baseline survey will be randomized with a 1:1:1 ratio in a block size of 3 into one of the three study arms generated using PASS 2023 [39]. Randomization will be stratified by cancer stage (1:1:1 non-metastatic vs. metastatic). Metastatic stage is defined by the presence of distant metastasis based on pathological, clinical, or lab findings, or by receipt of non-curative intent treatment. For hematologic malignancies, acute leukemias and stage IV lymphoma will be categorized under metastatic staging.

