#### FinEd

3.7.2

Patients will receive FinEd intervention within 4 weeks after enrollment. The intervention consists of mailing patients a packet including: (1) a comprehensive list of local resources that can help with food insecurity, transportation or living expenses; (2) contact information for national non-profit financial navigation organizations such as Patient Advocate Foundation where patients can self-refer. PAF provides case management and financial aid assistance to individuals facing chronic, life-threatening, and debilitating illnesses. [41], and (3) financial education materials in the format of brochures and videos with QR codes on topics such as understanding health insurance costs, how to read an explanation of benefits and medical bills, how to find care that is covered by insurance, how to use price estimator tool (brochure only), choosing a health plan (brochure only). The videos are developed by our research team using content from publicly available materials and input from a team of patients, patient educators, and community advisors working with our cancer center community outreach engagement team. After delivery of the intervention materials, a bilingual study coordinator will set up a one-time phone or zoom meeting with the participants to give an overview of resources shared, and answer patients’ questions. The study coordinator will complete a study-specific training under supervisor of a senior researcher on how to discuss the resources to ensure fidelity in delivery of intervention.

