**Methods: Assignment of interventions**			
Randomization:			
Sequence generation	21a	Who will generate the random allocation sequence and the method used	8
	21b	Type of randomization (simple or restricted) and details of any factors for stratification. To reduce predictability of a random sequence, other details of any planned restriction (e.g., blocking) should be provided in a separate document that is unavailable to those who enroll participants or assign interventions	8
Allocation concealment mechanism	22	Mechanism used to implement the random allocation sequence (e.g., central computer/telephone; sequentially numbered, opaque, sealed containers), describing any steps to conceal the sequence until interventions are assigned	8
Implementation	23	Whether the personnel who will enroll and those who will assign participants to the interventions will have access to the random allocation sequence	NA
Blinding	24a	Who will be blinded after assignment to interventions (e.g., participants, care providers, outcome assessors, data analysts)	5
	24b	If blinded, how blinding will be achieved and description of the similarity of interventions	NA
	24c	If blinded, circumstances under which unblinding is permissible, and procedure for revealing a participant's allocated intervention during the trial	NA

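### A fixed block of 3 for three arms lets anyone who knows two allocations in a block deduce the third, so concealment cannot be assured

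*Protocol article*

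**What the plan says.** The allocation rule is in section 3.6 (Randomization): patients who have consented and completed the baseline survey "will be randomized with a 1:1:1 ratio in a block size of 3 into one of the three study arms". The only stratification factor is stage: "Randomization will be stratified by cancer stage (1:1:1 non-metastatic vs. metastatic". There are thus two lists, and neither is divided by clinic or recruiter.

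Four other places describe who works around that rule:

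- Section 3.1 (Trial design): "There will be no blinding of participants or study coordinators".
- Section 3.4 (Pre-screening and outreach): "Patients will be approached both in person by bilingual research coordinators during oncology clinic visits and remotely through email outreach via REDCap".
- Section 3.5 (Baseline survey), on the step before consent: "Eligible patients will receive a study overview by a study coordinator".
- Section 3.7.2 (FinEd), on delivery of one arm: "a bilingual study coordinator will set up a one-time phone or zoom meeting with the participants".

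The SPIRIT checklist printed with the article says under item 21b that details of blocking "should be provided in a separate document that is unavailable to those who enroll participants or assign interventions". The article refers that item to page 8 and prints the block size.

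**The concern.** With three arms at 1:1:1, a block of 3 is the shortest possible and the most predictable. It is a single ordering of FinEd, EUC and CostCOM. Once two patients in a stratum's block have been allocated openly, the arm of the next one can be worked out by elimination. Hiding the list does not prevent this, because the deduction uses only past open allocations and the block size.

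The same group of staff approaches patients, explains the study before consent and delivers one arm without blinding. A coordinator who knows or suspects the next arm could, without intending it, hasten or delay the approach to a patient whose needs seem to suit that arm.

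Small shifts would count. Section 3.12.1 plans 30 patients per arm and anticipates a nonadherence proportion of 0.05 in an experimental arm. That is 0.05 × 30 = 1.5 expected events, and each patient is worth 1/30 = 3.3 percentage points. The trial is meant to supply initial efficacy estimates for a larger one, so any imbalance at entry would carry forward.

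**Working it through.** **The plan's own figures.** The article gives no figure for predictability. Its one calculation, Table 2 in section 3.12.1, reproduces to every printed digit (for n = 30 and p = 0.05 the one-sided 95% upper limit is 0.17251). Block size does not affect it.

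**Inputs.** Three arms, 1:1:1, block of 3, two stage strata (section 3.6); 90 patients (section 3.12.1); six clinics of one cancer center (section 3.2).

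**Best-guess rate under the fixed block of 3.** Assume the guesser knows every earlier allocation in the stratum and picks an arm not yet used in the block.

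- First place: 1/3
- Second place: 1/2 (one arm is ruled out)
- Third place: 1

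Mean = (1/3 + 1/2 + 1)/3 = 11/18 = 61.1%, or 55 of 90. Chance alone gives 1/3 = 33.3%, or 30 of 90.

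**Certain allocations.** These are the third places of complete blocks. For strata of size n1 and n2 the count is floor(n1/3) + floor(n2/3).

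| Split | Certain allocations |
|---|---|
| 45 / 45 | 15 + 15 = 30 |
| 30 / 60 | 10 + 20 = 30 |
| 40 / 50 | 13 + 16 = 29 |
| 44 / 46 | 14 + 15 = 29 |

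**Partial knowledge (assumption).** The article does not say how much each coordinator sees. Suppose the block boundaries are known and each of the two earlier allocations is known independently with probability q. The third is then deducible with probability q², so about 30q² are certain: 30 for q = 1, 30 × 0.5625 = 16.9 for q = 0.75, and 30 × 0.25 = 7.5 for q = 0.5.

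**Alternatives.** Fixed blocks were enumerated exactly. Mixed blocks were simulated as one list of 90, with sizes equally likely and a guesser who knows the set of sizes but not the current one.

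| Scheme | Best guess correct | Certain, of 90 |
|---|---|---|
| Fixed 3 (as planned) | 61.1% | 30 |
| Fixed 6, size known | 56.1% | 18 |
| Random 3 and 6 | 57.5% | 7.6 |
| Random 3, 6 and 9 | 55.3% | 3.5 |
| Random 6 and 9 | 54.1% | 4.6 |

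The guess rate falls only modestly. The main gain is in certain allocations: from 30 to 4.6, a cut of 25.4/30 = 85%.

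**The case against.** The strongest reply is that deducing an allocation in principle is not foreseeing it in practice. Lists are split by stage and not by clinic, so the two earlier patients in a block may have been seen at other clinics by other coordinators. CostCOM is delivered by a remote centralized navigator and EUC has no arm-specific session. No section says that one person recruits, delivers FinEd and keeps a running tally. This stands, and it is why 29 to 30 is a ceiling and not an expected count.

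Second, patients partly control when they enter the sequence. Outreach may be by email, consent by mail or REDCap, and a 30-minute survey must be finished before randomization. This makes it harder to steer a particular patient into a known place, but it leaves the timing of approach and consent open to influence.

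Third, a reader might infer that selection at entry could never be separated from treatment effect. The article does not support that. Nonadherence and other need measures are collected before randomization (section 3.5), Table 1 measures the primary outcome at baseline as a control, section 3.12.2 examines balance, and section 3.12.3 plans covariate regression. Measured imbalance can be seen and adjusted for; unmeasured selection cannot.

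A reader might also infer that concealment has failed. Nothing shows that steering occurred or that coordinators were told the block size during enrolment, and the item 21b wording is generic checklist text. Who generates the list and how assignments are released may properly sit in the full protocol, so their absence from a condensed article is not part of this point.

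**Conclusion.** The point holds as a stated design rule that is badly fixed. The third allocation of every complete block in each stage stratum is determined by the first two, and no other section offsets this. The ceiling is 29 to 30 certain allocations of 90 and a 61% best-guess rate against 33% by chance. Both figures assume a guesser who knows the block size and all earlier allocations in the stratum; with less knowledge they fall.

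The supportable conclusion is that concealment of upcoming assignments cannot be assured. The sample size and Table 2 are untouched. For a pilot whose product is preliminary estimates, this should be corrected while it still can be, but it does not invalidate the trial.

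**What to change.** The article does not state recruitment status, so the change depends on it.

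**If allocations remain to be made:** replace the fixed block of 3 with randomly varied permuted blocks, for example 6 and 9, within each stage stratum, and withhold the sizes from recruiting staff. Even if the set of sizes became known, about 5 of 90 allocations would be certain, scaled to a full list. The work is to regenerate the rest of the list and amend one sentence of section 3.6. The cost is some imbalance in arm sizes. An unfinished block of 9 can leave two arms 3 apart, so two strata can leave them at most 3 + 3 = 6 apart, against 1 + 1 = 2 now. That is minor for a trial that estimates proportions in about 30 patients per arm.

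**If enrolment is complete:** report the fixed block of 3 with unblinded recruiting staff as a limitation, and adjust the arm comparisons for the baseline value of the outcome and for stage. This costs little because both are already collected. It addresses measured imbalance only, and with about 1.5 events expected in an arm at the anticipated proportion, the adjusted estimate for the primary outcome will be imprecise.

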### Study arms

3.7

Patients in all arms will receive the usual care, which includes meeting with an institutional social worker upon provider referral due to patient-reported financial and HRSNs concerns during their oncology visits. For all patients, receipt of any institutional financial counseling or navigation will be extracted from EMR by the research coordinators at baseline, 3-, and 6 months after randomization.

#### Enhanced usual care (EUC)

3.7.1

Usual care will be enhanced by study-specific identification of patients with financial hardship and HRSNs facilitated by the study team. Patient's report of HRSNs or financial hardship will be documented in the study database and is not shared with the clinical team or integrated with the EMR. A prior study has shown screening for financial hardship ***alone*** may reduce the development or worsening of financial hardship [40].

#### FinEd

3.7.2

Patients will receive FinEd intervention within 4 weeks after enrollment. The intervention consists of mailing patients a packet including: (1) a comprehensive list of local resources that can help with food insecurity, transportation or living expenses; (2) contact information for national non-profit financial navigation organizations such as Patient Advocate Foundation where patients can self-refer. PAF provides case management and financial aid assistance to individuals facing chronic, life-threatening, and debilitating illnesses. [41], and (3) financial education materials in the format of brochures and videos with QR codes on topics such as understanding health insurance costs, how to read an explanation of benefits and medical bills, how to find care that is covered by insurance, how to use price estimator tool (brochure only), choosing a health plan (brochure only). The videos are developed by our research team using content from publicly available materials and input from a team of patients, patient educators, and community advisors working with our cancer center community outreach engagement team. After delivery of the intervention materials, a bilingual study coordinator will set up a one-time phone or zoom meeting with the participants to give an overview of resources shared, and answer patients’ questions. The study coordinator will complete a study-specific training under supervisor of a senior researcher on how to discuss the resources to ensure fidelity in delivery of intervention.

